#### Secondary analysis

By using appropriate tests, the secondary outcomes will be compared between study groups. The p-value and 99% CI will be generated for the treatment results.

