### Sample size

The sample size estimation of the main RCT was based on data from the ASPRE trial (6). The results of this trial showed that preterm PE occurred in 1.6% of the intervention group as compared with 4.3% in the placebo group. We calculated that the enrollment of 1792 participants in a 1:1 ratio of distribution (896 participants in each group) would provide the trial with a power of 90% (alpha level of 5%). If we are allowed a 10% loss to follow-up, the sample size will reach 986 participants in each group. A total of 1972 eligible participants will be randomly selected to participate in the trial arms. Furthermore, we proposed a sample size of 200 high-risk pregnancies in the pilot study and quality control. By screening 1686 pregnant women who attended the Maternal-Fetal hospital Clinic, we achieved this sample size. From January 2023, after obtaining written conscious consent, the trial began with 100 participants in each group at a 1:1 ratio, randomly.

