### Statistical analysis

For all primary analyses, the intervention group will be compared to the control group. Statistical analyses will be performed using STATA statistical software version 17.0 (STATA Corp, Texas, USA) and SPSS version 25 (SPSS, Inc., Chicago, IL, USA). Descriptive data will be reported as the mean 
±
 SD, median (IQR), or count (percent) as appropriate. The Shapiro-Wilk normality test will be applied to test the normality of the quantitative data. Continuous data will be compared between 2 groups using an independent sample *t* test or Mann-Whitney U test, and categorical data will be compared using the Chi-square test. Finally, to find the independent effect of aspirin treatment in high-risk participants a multiple logistic regression test will be used, in which the effect of aspirin treatment will be adjusted for the background variables of the participants that will differ between the 2 groups. The level of significance was 
<
 0.05. A complete set of descriptive statistics will be produced for all variables overall and by the treatment group. Graphical displays will be produced as appropriate.

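### Secondary outcomes are to be reported with 99% confidence intervals while the only stated significance level is 0.05, so the interval and the p-value do not match

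*Protocol article*

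**What the plan says.** Three places in the protocol article bear on the point.

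- **Statistical analysis.** After listing the t test, Mann-Whitney, chi-square and logistic regression, the section gives one threshold: "The level of significance was" below 0.05. It is not confined to any outcome.
- **Secondary analysis.** "By using appropriate tests, the secondary outcomes will be compared between study groups". The next sentence reads: "The p-value and 99% CI will be generated for the treatment results".
- **Sample size.** The trial is sized for 90% power at an alpha of 5%, from rates given as "preterm PE occurred in 1.6% of the intervention group as compared with 4.3% in the placebo group", leading to "enrollment of 1792 participants in a 1:1 ratio of distribution (896 participants in each group").

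The Secondary outcomes section lists eight outcomes, two of which (SGA requiring delivery, and spontaneous preterm delivery) are assessed at both <34 and <37 weeks. The article mentions neither a 0.01 level nor a multiplicity adjustment, and does not explain the 99% level.

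**The concern.** A two-sided p-value and a confidence interval from the same statistic agree on whether no effect is excluded only when the interval has level 1 minus alpha. Here alpha is 0.05 and the interval level is 99%. The same secondary result can therefore carry a p-value that counts as significant and an interval that includes a risk difference of 0 or a risk ratio of 1.

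What is at stake is the reading of abruption, SGA, stillbirth, preterm delivery, respiratory distress, ventilation, NICU admission and neonatal anomaly. A reader who takes an interval covering no effect as inconclusive would disagree with a report that applies the stated 0.05. The level that governs also matters for error control, because a 0.05 test and a 0.01 test over eight outcomes have very different chances of a false positive.

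**Working it through.** **Inputs.** Significance level 0.05 (Statistical analysis); interval level 99% (Secondary analysis); rates 4.3% and 1.6%, power 90%, alpha 5%, 896 per arm (Sample size); eight secondary outcomes (Secondary outcomes). The powers and event counts in steps 3 and 4 are assumptions.

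**1. Which alpha the plan uses.** Pooled-variance formula for two proportions, with d = 0.043 − 0.016 = 0.027 and mean rate 0.0295:

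n′ = [z(α)·√(2 × 0.0295 × 0.9705) + 1.2816·√(0.043 × 0.957 + 0.016 × 0.984)]² / 0.027²

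Two-sided 0.05: [1.960 × 0.2393 + 1.2816 × 0.2385]² / 0.000729 ≈ 823.2.

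Continuity correction: n = (n′/4)·[1 + √(1 + 4/(n′d))]² ≈ 895.8, which rounds up to the stated 896. One-sided 0.05 gives 671 without and about 743 with the correction, so it does not reproduce 896. The article does not state sidedness, but its own figure points to two-sided 0.05.

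**2. Where the two levels separate.** Two-sided p < 0.05 needs |z| > 1.960. A 99% interval excludes no effect only if |z| > 2.576. It is 2.576/1.960 = 1.314 times as wide as the 95% interval. For 1.960 < |z| < 2.576, that is 0.01 < p < 0.05, the result is significant but the interval covers no effect. At p = 0.02 (z = 2.326), the limit lies 2.576 − 2.326 = 0.25 standard errors beyond no effect.

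**3. How often this happens.** For a normal test statistic:

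- No effect: 0.05 − 0.01 = 4% of tests.
- True effect with 80% power at 0.05: the mean of z is 1.960 + 0.842 = 2.802. The chance is Φ(2.802 − 1.960) − Φ(2.802 − 2.576) = 0.800 − 0.589 = 21%.
- With 90% power the same calculation gives 15%.

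**4. Illustration with assumed counts.** A secondary outcome in 30/896 versus 50/896:

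- Chi-square p = 0.022 (0.030 with continuity correction).
- Risk difference −2.2 points, standard error 0.974 points.
- 95% interval: −2.2 ± 1.960 × 0.974, that is −4.1 to −0.3.
- 99% interval: −2.2 ± 2.576 × 0.974, that is −4.7 to +0.3.
- Risk ratio 0.60: 95% interval 0.39 to 0.93; 99% interval 0.34 to 1.07.

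On either scale the result is significant at 0.05 and the planned 99% interval includes no effect.

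**5. What turns on the level.** For eight independent true null hypotheses, the chance of at least one false positive is 1 − 0.95⁸ = 34% at 0.05 and 1 − 0.99⁸ = 7.7% at 0.01. Independence is an assumption, and these outcomes are likely to be correlated.

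**The case against.** The strongest reply is that the article contains only one decision rule. Significance is judged by p < 0.05; the Secondary analysis section merely says that an interval will be produced, and never makes its coverage of no effect a second test. That is correct. A reader might infer that the plan has two competing rules, or none that decides between them, and the text does not support either reading. What remains is a stated interval level that does not match the stated test level.

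A reader might also carry the 99% level over to the primary outcome and conclude that the trial is too small: the formula above at two-sided 0.01 gives about 1239 per arm. The documents do not support this. The sentence stands under the Secondary analysis heading, directly after one about secondary outcomes, and the sample size is built on 5%.

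A further inference is that investigators could pick the level after seeing the data, since the Monitoring section gives researchers access to results at any stage. The Blinding section, however, provides for an analyst blind to allocation (loosely worded), and both the p-value and the interval are to be reported, so a reader could roughly rescale the interval.

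Finally, 99% may be a deliberate guard against multiplicity, explained in an analysis plan that is not shown. That is possible, and a missing rationale alone would not be a finding. But the article itself states both levels, and with 0.05 as the only threshold a wider interval does not change what is called significant.

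**Conclusion.** The point holds as a mismatch between two stated levels, confined to secondary outcomes. For p between about 0.01 and 0.05, a secondary result is significant by the Statistical analysis section while the interval planned in the Secondary analysis section includes no effect. The size is 4% of tests under no effect and about 21% for an effect with 80% power at 0.05. The first figure follows from the two levels alone. The second rests on an assumed power and a normal test statistic.

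The boundary at 0.01 is approximate, because test and interval may come from different statistics. With 30/896 versus 54/896, for example, the continuity-corrected p is 0.0102, yet the 99% Wald interval for the risk difference (−5.2 to −0.1 points) excludes no effect. This affects only results close to 0.01.

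The primary analysis and the 896 per arm stand as far as this point goes. It is a modest inconsistency, but it affects what can be claimed for eight outcomes, and it should be settled before the outcome data are analysed.

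**What to change.** Match the two levels for secondary outcomes. The article does not reveal the intent, so the sponsor should choose between two options:

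- **Option A.** Change the Secondary analysis section to 95% intervals, in agreement with the existing 0.05. This is the smaller edit. It leaves the secondary outcomes without any multiplicity protection in the article.
- **Option B.** If 99% was meant as protection over the eight listed outcomes, keep it. State p < 0.01 (two-sided) as the secondary threshold, and say that 0.05 with a 95% interval applies to the primary outcome. The price is that secondary results with p between 0.01 and 0.05 can no longer be called significant.

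Either option takes a sentence or two in the statistical section and leaves the design and the sample size unchanged.

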## 3. Discussion

Trophoblastic invasion into the myometrium portion of the spiral arterioles during normal placentation is performed in a 2-stage process. It starts at 6–8 wk of gestation and culminates at 16–20 wk. During this process, the spiral arteries are replaced with wide nonmuscular channels insensitive to vasomotor control. Incomplete deep placentation has been associated with a spectrum of pregnancy complications including PE (19).

PE is caused by the inability of trophoblast cells to invade the spiral arteries of the myometrial layer. Lyall and colleagues found that vascular spasms and inefficient blood circulation inside the fetoplacental unit are caused by ineffective trophoblast invasion (20).

The incidence of disease may be halved by LDA consumption before 16 wk of gestation (21). In one systematic review study, aspirin reduces the risk of preterm PE only when initiated at 16 wk of gestation and taken at a daily dose of 100 mg, but not term PE (22). Meta-analysis recommended that aspirin use before 17 wk decreases the risk of PE in SGA neonates (23). The mechanism of aspirin remains obscure, but it could include recovery of the alteration of uterine spiral arteries (22, 23). The level of platelet activation in pregnant women with PE is significantly higher than that in pregnant women without PE. This is shown by a shortened activated partial thromboplastin time and a hypercoagulable state. Aspirin can help regulate the balance between thromboxane and prostacyclin, and can also inhibit platelet aggregation. This can prevent the formation of small blood clots, reduce damage to organs caused by blood clots, and help to prevent PE (4, 5, 24).

Other studies found LDA improves altered cytokine production and has positive effects on sFTL1 production (9, 10).

We designed an RCT to investigate whether the earlier administration of aspirin from the first stage of spiral arteries invasion in the process of the placentation could further reduce the incidence of PE. We also speculate that aspirin administration at the same time as the spiral arteries transformation may be more effective in the prevention of PE and other complications related to these vessel disorders. In addition, this trial was designed to compare the effectiveness of aspirin administration at this time versus administration after 11 wk to prevent early and late-onset PE.

### Strengths and limitations of the trial

1. This is the large single-center RCT to compare the effect of aspirin administration from early pregnancy versus after 11 wk in women at risk of PE.

2. Screening and start of prevention with aspirin from the early stage of pregnancy in high-risk women can provide an opportunity for more effective prevention of PE.

3. Follow-up of newborns is only confined to the primary postnatal period for the time of stay in the hospital.

##  Data availability

Following the completion of the study, information used will be obtained from the corresponding author upon rational request.
